## Abstract

**Background:**

Traditionally, medical students have learned surgical skills by observing a resident physician or surgeon who is performing the technique. Due to inconsistent practice opportunities in the clinical setting, a disparity of skill levels among students has been observed. In addition, the poor availability of faculty professors is a limiting factor in teaching and adequately preparing medical students for their clerkship years. With the ongoing COVID-19 pandemic, medical students do not have access to traditional suturing learning opportunities. Didactic courses are available on videoconferencing platforms; however, these courses do not include technical training.

**Objective:**

Our overarching goal is to evaluate the efficacy and usability of web-based peer-learning for advanced suturing techniques (ie, running subcuticular sutures). We will use the Gamified Educational Network (GEN), a newly developed web-based learning tool. We will assess students’ ability to identify and perform the correct technique. We will also assess the students’ satisfaction with regard to GEN.

**Methods:**

We will conduct a prospective randomized controlled trial with blinding of expert examiners. First-year medical students in the Faculty of Medicine of Université de Montréal will be randomized into four groups: (1) control, (2) self-learning, (3) peer-learning, and (4) peer-learning with expert feedback. Each arm will have 15 participants who will learn how to perform running subcuticular sutures through videos on GEN. For our primary outcome, the students’ ability to identify the correct technique will be evaluated before and after the intervention on GEN. The students will view eight videos and rate the surgical techniques using the Objective Structured Assessment of Technical Skills Global Rating Scale and the Subcuticular Suture Checklist as evaluation criteria. For our secondary outcomes, students will anonymously record themselves performing a running subcuticular suture and will be evaluated using the same scales. Then, a survey will be sent to assess the students’ acceptance of the intervention.

**Results:**

The study will be conducted in accordance with the Declaration of Helsinki and has been approved by our institutional review board (CERSES 20-068-D). No participants have been recruited yet.

**Conclusions:**

Peer learning through GEN has the potential to overcome significant limitations related to the COVID-19 pandemic and the lack of availability of faculty professors. Further, a decrease of the anxiety related to traditional suturing classes can be expected. We aim to create an innovative and sustainable method of teaching surgical skills to improve the efficiency and quality of surgical training in medical faculties. In the context of the COVID-19 pandemic, the need for such tools is imperative.

**Trial Registration:**

ClinicalTrials.gov NCT04425499; https://clinicaltrials.gov/ct2/show/NCT04425499

**International Registered Report Identifier (IRRID):**

PRR1-10.2196/21273

## Introduction

The necessity for medical students to develop proper suturing skills to achieve future excellence in surgery is sufficiently important to warrant interest in pursuing educational research with the goal of implementing systematic and effective methods of training [1]. Historically, the traditional methods by which medical students learn basic suturing skills have involved observation and trial during clerkship [2-4]. Currently, several issues pertaining to this practice in medicine have arisen due to the legal ethics involved [5] because both patients and students are at greater risk of injury. Without appropriate preparation, students are at higher risks of making mistakes [1,6]. Poor suturing technique and increased wound tension have been associated with substandard wound adhesion and increased scar formation [7]. The levels of comfort, confidence, and preparedness felt by medical students when performing these medical acts are also less developed [8], which may further adversely affect their performance when treating a real patient.

The academic learning objectives of medical students include several different suturing techniques. The most basic is the simple interrupted suture. A more advanced technique is the running subcuticular suture. All medical students are required to learn these surgical skills during their education, which is a source of anxiety and a challenge for many students.

With the traditional method, student learning depends on circumstances and the random presentation of cases [6]. The benefits of developing basic surgical skills before clerkship have been demonstrated. Early and prolonged exposure to and practice of suturing have been associated with an increased level of confidence relative to suturing a patient [2,4].

Acquiring this skill during preclinical years may increase the level of preparation of students, thereby increasing the professionalism and quality of the medical acts they perform on patients. However, the training in this technique during preclinical years has been limited due to time constraints on faculty staff as well as the cost of using these staff as trainers [9,10].

Several studies support peer-assisted training during preclinical years as a sustainable alternative [9,11-14]. These studies focus on basic surgical skills, such as uninterrupted stitches and knot-tying [15]. Although most studies demonstrate equivalence in acquisition of proficiency whether students are taught by peers or by faculty surgeons [12,13,16-18], it is unknown whether these results can be extrapolated to more advanced suturing skills, such as the vertical/horizontal mattress or running subcuticular sutures. In 2013, a study compared the execution of interrupted and subcuticular sutures among three groups: expert-trained, peer-trained, and self-taught. This study demonstrated that the execution by students in the peer-trained group was equivalent to that of the expert-trained students for both suture techniques [8]. Further studies pertaining to more advanced skills are warranted.

In the pursuit of developing sustainable alternatives in surgical education, several web-based tools have been gaining ground; tools that implement gamification elements are of particular interest, as they may further engage the student during their learning experience [19-21]. Several publications support gamified learning in health education due to its many unique advantages. Innovative platforms have the potential to provide effective, collaborative, inexpensive, and enjoyable opportunities to learn [19,21,22]. The Gamified Educational Network (GEN) is a web-based platform that was developed at Ontario Tech University and permits peer feedback through video assessment. Several educational tools have been developed and tested in surgical training [23-27]; however, the GEN platform enables students to learn a variety of skills without developing incorrect habits while practicing on their own. Students can upload videos of themselves performing a skill and share improvement tips with peers. Long-term retention of a surgical skill is optimal when the training is spread out over time rather than being provided in a single training session in one day [28]. Therefore, this platform offers superior psychomotor skill development by offering students the opportunity to expand the practice time of basic surgical skills beyond the classroom or clinical setting. In this way, students can practice skills and receive direct feedback at home.

During the present worldwide event of the COVID-19 pandemic, medical curricula have been suspended [29-31]. Therefore, offering students access to optimally efficient academic tools at home is of primordial importance [32]. The necessity for video instruction investigations is henceforth essential.

This study has four aims: (1) to evaluate students’ ability to identify the correct subcuticular suture method, comparing three web-based learning approaches of self-learning, peer-learning, and peer-learning with expert feedback; (2) to evaluate students’ ability to execute a proper running subcuticular suture, comparing three web-based learning approaches of self-learning, peer-learning, and peer-learning with expert feedback; (3) to determine the students’ acceptance of GEN to improve the platform as a learning tool; and (4) to develop an innovative web-based training and teaching method to better prepare students for simulation training and clerkship.

## Methods

### Study Design

This will be a prospective randomized controlled study with blinding of expert examiners. The study has been registered (ClinicalTrials.gov NCT04425499).

### Population

Participants are first-year medical students at Université de Montréal. We decided to target this population because these students do not yet have significant experience with suturing. We will invite the whole cohort (about 300 students) by email. 

### Eligibility and Ineligibility Criteria

#### Conditions for Eligibility

Students must be enrolled in their first year of medical school at Université de Montréal.

#### Conditions for Ineligibility

Students will be ineligible if they have returned after a leave, such as a sabbatical year, sick leave, or maternity leave; have already obtained a medical degree in another country; have studied medicine in another country; or are injured at the beginning of the study.

### Participant Recruitment

All students in their first year of medical school will receive an email inviting them to participate in the study. If they agree, they will be required to complete a consent form and provide a mailing address (Qualtrics XM).

All students enrolled in this study will be asked to participate using a personal computer. Students will be advised that participation will require their availability for one to three hours on three consecutive days. They will be advised not to study, practice, or view any external videos pertaining to suturing skills for the duration of the study.

When the students agree to participate, they will receive an email with the GEN platform link.

Students' previous experience with suturing will be surveyed, as well as the context of this experience (eg, workshop, former profession).

Upon creation of a new user account on GEN, students will be automatically randomized to one of the four groups and will only have access to the platform set for their study group.

### Randomized Groups and Study Intervention

Figure 1 depicts the study intervention.

**Figure 1 figure1:**
[figure not shown]
Study workflow. GEN: Gamified Educational Network; GRS: Global Rating Score.

#### Group 1: Control Group

On GEN, each student will individually view eight videos of an expert performing a running subcuticular suture correctly as a pretest. The Objective Structured Assessment of Technical Skills (OSATS) Global Rating Scale (GRS) (Table 1) and Subcuticular Suture Checklist (Textbox 1) will be made available beside each video, and students will be required to fill out these assessments for each video. For three days, students will have access to a distinct set of videos on GEN to learn running subcuticular sutures. Three days later, each student will perform a subcuticular suture on a suturing pad and record their first attempt. Then, students will undergo a posttest with the same eight videos shuffled in a different order. The order of the videos will be the same for all students.

The OSATS, developed by the University of Toronto, is an accurate and validated method of assessing surgical skills in an operating room setting [33,34]. It comprises a GRS (Table 1) in which certain skills are graded from 1 to 5 (ie, respect for tissue, time in motion, knowledge of instruments, instrument handling, suture skill, flow of operation, knowledge of procedures, and final product).

The checklist is a list of verifications specific to the technique of interest to ascertain whether every step of the procedure was executed (Textbox 1). The checklist was built and revised by a focus group led by the principal investigator, who is the director of the clerkship surgical rotation in the Faculty of Medicine of Université de Montréal. The focus group was composed of one medical student, one junior surgery resident, and one senior surgery resident.

**Table 1 table1:** Global Rating Scores of the Objective Structured Assessment of Technical Skills [8,33,34]. The students will be asked to rate the candidate’s performance on a scale of 1 to 5, and the total score will be summed.

Skill	Potential scores for observed outcomes				
	1-2		3		4-5
Respect for tissue	Frequently used unnecessary force on tissues or caused damage by inappropriate instrument use		Careful handling of tissue, but occasional inadvertent damage		Consistently handled tissues appropriately with minimal damage
Time in motion	Many unnecessary moves		Efficient time and motion, but some unnecessary moves		Clear economy of movement and maximum efficiency
Instrument handling	Repeatedly makes tentative or awkward moves with instruments		Competent use of instruments, but occasionally awkward		Fluid movements
Suture skill	Awkward and unsure with poor knot tying and inability to maintain tension		Competent suturing with good knot placement and appropriate tension		Excellent suture control with correct suture placement and tension
Flow of operation	Frequently stopped operating, seemed unsure of next move		Demonstrated some forward planning and reasonable progression of procedure		Obviously planned operation
Knowledge of procedure	Inefficient knowledge of procedure. Looked unsure and hesitant		Knew all important steps of procedure		Demonstrated familiarity of all steps of procedure
Final product	Final product of unacceptable quality		Final product of average quality		Final product of superior quality
Overall performance	Very poor		Competent		Very good

Subcuticular suture checklist. One point is given for each step performed correctly.

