#### Group 2: Self-Learning

Each student will view eight videos individually and complete the GRS and Subcuticular Suture Checklist for each video as a pretest. Six videos will contain errors and two videos will not. The errors will be technical mistakes in the execution of a running subcuticular suture. Then, for three days, students will have access to a distinct set of videos on GEN to learn how to perform running subcuticular sutures. Three days later, each student will perform a subcuticular suture on a suturing pad and record their first attempt. Finally, students will perform a posttest with the same eight videos shuffled in a different order. The order of the videos will be the same for all students.

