#### Group 3: Peer-Learning

Each student will view eight videos and complete the GRS and Subcuticular Suture Checklist for each video as a pretest. Six videos will contain errors and two videos will not. After this initial test, students will interact with other medical students in their group on the GEN platform anonymously for three days. We will display distinct videos on GEN. Comments will be allowed in an interactive format to encourage exchanges. Students will be required to participate in the discussion of at least two videos. Students will not be able to modify their answers on the initial test. Three days later, each student will perform a subcuticular suture on a suturing pad and record their first attempt. Students will interact on GEN and comment on the videos recorded by their peers. On the third day, the students in this group will perform a posttest with the same eight initial videos, but shuffled. The order of the videos will be the same for all students.

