### Study Procedure

#### Objective 1: Evaluate Students’ Ability to Identify the Correct Subcuticular Suture Method

We will determine the best learning method in a virtual environment among the three main groups. We will compare groups 2, 3, and 4: self-learning, peer-learning, and peer learning with expert feedback. There will be no crossovers. Students will undergo a pretest and a posttest to assess the effect of the intervention on their ability to identify the correct way to perform subcuticular sutures. We will also use the control group to compare our intervention to the regular web-based learning method, in which students learn alone by watching different videos with no artificial errors inserted. We will analyze the students’ scoring of each video with the GRS and Subcuticular Suture Checklist.

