#### Pretest and Posttest

All videos will show an expert performing a running subcuticular suture. The expert will be an experienced faculty surgeon licensed by the Royal College of Canada. The expert will only perform the suture without explanation; there will be no sound accompanying the videos. Among the eight videos displayed to students in groups 2, 3, and 4, six will contain technical errors. We will evaluate the students’ ability to identify the errors as they complete the GRS and the Subcuticular Suture Checklist. Participants in groups 2, 3, and 4 will all see the same videos in the same order. The OSATS GRS (Table 1) and Subcuticular Suture Checklist (Textbox 1) will be available beside each video in the pretest and posttest for every student in all four groups.

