### Statistical Analysis Plan

First, we will perform descriptive statistical analyses to assess the distributions of the variables of interest and determine the appropriate tests to use as well as the need for a potential transformation. Continuous variables with an asymmetric distribution will be described using median (IQR). Categorical variables will be described with proportions. The remaining variables will be described with mean (SD).

In the following paragraphs, we describe our statistical plan assuming a Gaussian distribution.

Objective 1: We will perform balanced one-way ANOVA to compare mean GRS and Subcuticular Suture Checklist scores among all four groups. First, distinct analyses of the pretest and the posttest scores will be performed. Then, the mean difference between the pretest and the posttest scores will be compared using paired *t* tests if the difference between paired values is consistent.

Objective 2: We will perform balanced one-way ANOVA to compare the performance of students in executing a running subcuticular suture as assessed by the GRS and the Subcuticular Suture Checklist.

Objective 3: We will perform descriptive statistical analyses and correlate the study groups with the Likert scales using the Kruskal-Wallis equality-of-population rank test.

Analysis will be performed in RStudio version 1.2.5033 (RStudio Team) [36] and GraphPad Prism version 8.0.0 for Mac OS X (GraphPad Software) [37]. For each analysis, confidence intervals will be calculated for a 95% confidence level. Statistical hypothesis testing will be performed with an alpha threshold of .05.

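### On Objective 1 the control arm rates error-free test videos while groups 2-4 rate a set with six faulty videos of eight, so the four-group ANOVA and every contrast with control mix test content with learning method

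*Protocol article*

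**What the plan says.** All statements are from the protocol article.

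- **Control, test videos** (Group 1: Control Group): "each student will individually view eight videos of an expert performing a running subcuticular suture correctly as a pretest". After the learning period, "students will undergo a posttest with the same eight videos shuffled in a different order".
- **Groups 2 and 3, test videos** (Group 2: Self-Learning; Group 3: Peer-Learning): "Six videos will contain errors and two videos will not. The errors will be technical mistakes in the execution of a running subcuticular suture"; "Six videos will contain errors and two videos will not. After this initial test, students will interact with other medical students". Group 4 is described as mostly the same as group 3.
- **Pretest and Posttest**: "Among the eight videos displayed to students in groups 2, 3, and 4, six will contain technical errors". The statement of a common test is limited to three arms: "Participants in groups 2, 3, and 4 will all see the same videos in the same order". The purpose given there is to see whether students find the errors while completing the two scales.
- **Objective 1**: "We will compare groups 2, 3, and 4: self-learning, peer-learning, and peer learning with expert feedback". The same paragraph adds that the control group will also be used, as regular web-based learning with no artificial errors in the videos.
- **Statistical Analysis Plan, Objective 1**: "We will perform balanced one-way ANOVA to compare mean GRS and Subcuticular Suture Checklist scores among all four groups". Pretest and posttest are analysed separately, followed by a pretest-posttest comparison.

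The article describes no score against a reference rating and no adjustment for the different video content.

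**The concern.** The analysed variable is the rating that a student gives to the test videos. A good rater should give high marks to eight correct performances and lower marks to a set in which six are faulty. A gap between control and the other arms is therefore expected even if all students are equally able, and it may be present at pretest, before any learning. Randomization does not remove it, because the instrument itself differs by arm.

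The learning phases of groups 1 and 2 are described in almost the same terms: individual access for three days to a distinct set of videos, with no peer feedback. On Objective 1 their only documented difference is thus the test set.

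At stake is the planned primary F test, on which the trial was sized. It could be significant because of test content alone and be reported as a difference between learning methods.

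**Working it through.** **Step 1. The test sets side by side.**

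| Arm | Test videos with errors | Without errors |
|---|---|---|
| 1 Control | 0 | 8 |
| 2, 3, 4 | 6 | 2 |

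**Step 2. The plan's own sample size.** The Sample Size section gives a four-group one-way ANOVA, effect size 0.8 (metric not named), within-group SD 1.45, power 80%, alpha 0.05, and a result of 13 per group. Reading 0.8 as the between-group SD, the noncentrality is λ = (k − 1) × n × 0.8² / 1.45² = 3 × 13 × 0.64 / 2.1025 = 11.87. Power is 80.2% at n = 13 and 76.2% at n = 12, so 13 is reproduced. This reading is inferred. The sample size is not the problem here; it is needed for the cost of the fix.

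**Step 3. Size of the artefact on the checklist.** Inputs from the document: 24 checklist items at one point each, 1 to 3 errors per faulty video, 15 students per arm. Assumptions: each detected error costs one checklist point, and points wrongly withheld are equally frequent in all arms. The gap in mean score per video between control and groups 2-4 is

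shift = 6 × (errors per faulty video) × (proportion detected) / 8.

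With all errors detected this is 0.75, 1.5 or 2.25 points for 1, 2 or 3 errors. With half detected it is 0.375, 0.75 or 1.125.

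**Step 4. Probability that the four-group F test rejects with no ability difference.** When one arm of four is shifted by d = shift/SD, f = d × √3/4 and λ = 60 × f², with 3 and 56 degrees of freedom. For example, a shift of 1.5 with SD 1.45 gives d = 1.034, f = 0.448, λ = 12.04 and a rejection probability of 81%.

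| SD | Detected | 1 error | 2 errors | 3 errors |
|---|---|---|---|---|
| 1.45 | all | 26% | 81% | 99% |
| 1.45 | half | 9.5% | 26% | 54% |
| 3.0 | all | 9% | 24% | 51% |
| 3.0 | half | 6% | 9% | 15% |

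The nominal level is 5%. SD 1.45 is the document's figure for the GRS in an external study, borrowed here for the checklist; SD 3.0 is an assumed wider value. These probabilities apply to the separate pretest and posttest ANOVAs.

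**Step 5. Does the change score remove it?** Only if the offset is constant. Suppose that students in every arm improve equally, from detecting half of the errors to detecting all, with two errors per faulty video. The offset grows from 0.75 to 1.5 points: ratings in groups 2-4 fall by 0.75, while control, with no errors to find, does not change on this account. Equal learning then appears as a difference in change.

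**Step 6. Power if only groups 2-4 are tested.** With the inputs of step 2 and k = 3, λ = 2 × 15 × 0.64 / 2.1025 = 9.13 and power is 74.5% at 15 per group; 17 per group are needed for 80% (80.4%). With four groups on one common test, 15 per group give 86.4%.

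**The case against.** The strongest reply is that the core of Objective 1 is intact. The stated aim compares self-learning, peer-learning and peer-learning with expert feedback, and the Objective 1 section calls these the three main groups. They see the same videos in the same order. This stands: contrasts among groups 2, 3 and 4 are valid. A reader might infer that the whole primary outcome fails, and the document does not support that.

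A reader might also infer that the Objective 1 section already confines the analysis to groups 2-4 and so contradicts the analysis plan. It does not: the same paragraph plans a comparison with control. Dropping that comparison is a change of plan.

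The large rejection probabilities are open to challenge, and the challenge largely stands. The Study Limitations section expects poor suturing knowledge, so full detection is close to a ceiling. Some listed errors, such as excessive forceps force or unnecessary extra steps, have no clear checklist item, so even the shift for one error is not a floor. The SD is borrowed, and nothing was computed on the GRS.

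It can also be said that control students may still improve, since the outcome is worded as identifying the correct technique and they can learn to credit correct steps. That is fair, but their test cannot show improvement in finding errors, which is what the Pretest and Posttest section sets out to evaluate.

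Finally, the error content may be meant as part of the intervention. The article places it in the test videos, so exposure and measurement would then be the same object and could not be separated.

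**Conclusion.** The concern holds for the four-group ANOVA of raw ratings and for every Objective 1 contrast with control: test content and learning method are confounded, and change scores do not fully repair this. It does not extend to contrasts among groups 2, 3 and 4, nor to Objective 2, where all arms perform the same task and are scored on it.

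That the confounding exists follows from the text alone. Its size does not: the illustrated rejection probabilities run from 6% to 99%, and the 81% and 99% figures need full detection, one checklist point per error and the borrowed SD of 1.45. Because the affected test is the one specified for the primary objective, it should be settled before recruitment; the article states that no participants have been recruited.

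**What to change.** **Recommended change.** In the Statistical Analysis Plan, make the comparison of groups 2, 3 and 4 the inferential analysis for Objective 1. Report control ratings descriptively, and use the control arm inferentially only for Objective 2.

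*Cost.* The comparison with control that the Objective 1 section plans is given up. The power statement must also be rewritten: under the inferred reading that reproduces 13 per group, three groups of 15 give about 74.5%, and 17 per group would be needed for 80%. The sponsor should either accept the lower figure openly or enlarge these groups, and should name the effect-size metric.

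**Alternative, if the control contrast is to be kept.** Give all four arms the same eight-video pretest and posttest, six with errors and two without. The four-group sample size then stands, and the test set is needed for groups 2-4 in any case. The article says only that these videos will be recorded beforehand, so it should not be assumed that they already exist.

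*Cost.* With a common test and the learning phases left as described, groups 1 and 2 become the same arm. The protocol would have to state what distinguishes them during learning. The article calls the learning videos only distinct and does not say that groups 2-4 learn from faulty ones, so this may require new material and would be a change to the intervention, not only to the test.
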